#### Severity of anxiety and depressive symptoms

The Generalized Anxiety Disorder Scale (GAD-7) [84] and the Patient Health Questionnaire Depression Scale (PHQ-9) is used to assess severity of anxiety and depression, respectively [85].

#### Blood pressure (BP)

Systolic and diastolic blood pressure is measured using a standardized protocol. Two measurements are taken and the average of the two readings is calculated [86, 87]. Hypertension is defined as elevated blood pressure (average systolic BP (SBP) ≥ 140 mmHg and/or an average diastolic BP (DBP) ≥90 mmHg) or higher levels of hypertension if SBP ≥ 160 mmHg and/or an DBP ≥ 95 mmHg.

*Body Mass* Index (BMI) is calculated as weight (kg) divided by height (m^2^) [78]. Waist circumference is measured in centimeters.

#### Measures of diabetes and cardiac risk

Lipids (total cholesterol, LDL, HDL and triglycerides), *kidney function* (serum creatinine, urine creatinine and urine microalbumin) and glycemic control (HbA1c) are measured using standard assays. Dyslipidemia are defined as: LDL > 130 or HDL < 40 mg/dL [88]. We selected HbA1c because it is not affected by short-term dietary changes and strongly correlates with disease severity [89].

### Collaborative care PHC staff training outcome measures

Knowledge and Skills related to collaborative care are assessed using clinical vignettes followed by a set of questions on CMD and CVD screening, treatment, case management, communication, & use of consultation and referrals, tailored to each type of health professional at the PMC. Vignettes are effective in evaluating the benefits of training [90–93] including mental health training among primary care physicians in India [94].

#### Patient perceptions

To minimize socially desirable responses [95], we developed and administer a behaviorally anchored measure that targets patient perceptions of staff in terms of 1) patient interactions; 2) providing relevant information; 3) active listening and answering questions; and 4) addressing risk behaviors.

All data collected in interviews and laboratory tests are de-identified and uploaded to an encrypted password protected database. Double data entry occurs within 3 days of data collection. The data are monitored on an ongoing basis for completeness and accuracy.

### Statistical analyses

Preliminary analyses will include examination of the reliability of scales (e.g. PHQ-9, GAD-7), attrition analyses to compare respondents with complete data to those who do not complete the study with regard to group assignment and baseline demographics, and comparisons between the two intervention arms, to check for group balance. We will use chi-square tests for unordered categorical variables, Kruskal Wallis tests for ordinal or non-normal continuous data, and ANOVA for normal continuous variables.

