**Methods:**

This study is a multi-level randomized controlled trial among patients with depression or anxiety and co-morbid diabetes, or cardiovascular disease. Aim 1 examines whether patients screened at community health-fairs are more likely to be diagnosed and treated for these co-morbid conditions than patients screened after presenting at PHCs. Aim 2 evaluates the impact of collaborative care compared to usual care in a cluster RCT, randomizing at the level of the PHCs. Intervention arm PHC staff are trained in mental health diagnoses, treatment, and the collaborative care model. The intervention also involves community-based “Healthy Living groups” co-led by Ashas, using cognitive-behavioral strategies to promote healthy behaviors. The primary outcome is severity of common mental disorders, with secondary outcomes being diabetes and cardiovascular risk, staff knowledge and patient perceptions.

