#### Intervention

The primary, intention-to-treat (ITT) analyses will evaluate the impact of the intervention, both in terms of a) return to below-threshold levels for CMD and CVD/DM risk (i.e. dichotomized outcomes), and b) improvement in the levels of the continuous CMD and CVD/DM measures (depression and anxiety scores, BP, HbA1c, LDL, and serum creatinine levels) via logistic and linear mixed-effects regression models respectively, with repeated measures nested within individuals, and individuals nested within PHC, and random intercepts for individuals and PHC [96, 97]. The trajectories of the continuous variables will be examined via the time-by-intervention interaction effect. We will run separate regressions for the various outcomes, to allow us to detect if different variables react to the intervention at different rates. To prevent Type I error inflation, we will lower α accordingly. In all models covariates will be included as necessary.

The sample size of 1250 in each intervention arm (50 participants per PHC), was determined based on achieving 80% power for the ITT analyses regarding the effect of the intervention, and was calculated as follows: we assumed an attrition rate of 20%, and an intra-class correlation (ICC) of 0.1 to account for clustering of participants in PHCs, which reduces the initial sample size to an effective sample size of *n* = 204/group. Pooling data across the three post-intervention measurements triples this number, and subsequent adjustment for repeated measures with an assumed ICC = 0.5, results in a final *effective* sample size of *n* = 306 person-time observations per group. Based on previous research, we assumed 40% of control group participants to recover [98, 99]. With α = .025, the minimum detectable effect size at 80% power is 12% more of the intervention group participants recovering [100]. This is a small effect size according to Cohen [101], and comparable to earlier studies in the US [26]. To test the screening hypothesis, with 25 PHCs per screening condition, 80% power and α = 0.05, the minimum detectable effect in a Poisson regression is 2.1 times as many co-morbid cases identified with the enhanced compared to the standard screening [102]. Although this is a large effect, we deemed it attainable, given the documented under-reporting of mental health in standard care [10, 11], and the intensive nature of our enhanced screening.

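### Between-arm balance and attrition-by-arm tests ignore PHC clustering, so their p-values will be too small wherever the variable or attrition clusters by PHC

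*Protocol article*

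**What the plan says.** The opening paragraph of Statistical analyses in the protocol article sets out two preliminary checks. One is "attrition analyses to compare respondents with complete data to those who do not complete the study with regard to group assignment and baseline demographics". The other is "comparisons between the two intervention arms, to check for group balance". For both it names the tests: "We will use chi-square tests for unordered categorical variables, Kruskal Wallis tests for ordinal or non-normal continuous data, and ANOVA for normal continuous variables". It mentions no term, adjustment or unit of analysis for PHC.

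The design is clustered. The abstract states: "Aim 2 evaluates the impact of collaborative care compared to usual care in a cluster RCT, randomizing at the level of the PHCs". Setting and randomization describes allocation of the 50 PHCs. The sample-size paragraph under Intervention gives "The sample size of 1250 in each intervention arm (50 participants per PHC" and then: "we assumed an attrition rate of 20%, and an intra-class correlation (ICC) of 0.1 to account for clustering of participants in PHCs".

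The other analyses do allow for PHC. Under Screening, the count of identified cases is analysed with PHC as the unit, and linkage and retention with a mixed logistic model that has a PHC random intercept. Under Intervention, the primary models have random intercepts for individuals and for PHC. On covariates, the same section says only: "In all models covariates will be included as necessary".

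**The concern.** The article names specific tests that do not match the unit of randomisation, so this is a stated method and not merely a detail left to a fuller document. Participants of one PHC share a catchment area, staff and recruitment route. Where a variable clusters by PHC, the difference between arms varies more than an independent-sample test allows, and its p-value is too small.

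The contrast with the rest of the article is plain. Retention by place of first screening gets a PHC random intercept, but attrition by treatment group gets an ordinary test.

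What is at stake is mainly reporting. The trial could describe differences in baseline variables or in loss to follow-up as statistically significant when they are unremarkable for 25 PHCs against 25. Apparent differential attrition matters most, because participants and intervention staff are unblinded and 20% loss is planned for. Readers would take such a finding as a warning of bias.

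**Working it through.** **Inputs from the article.** 1250 participants per arm, 50 per PHC, so 1250/50 = 25 PHCs per arm; 20% attrition; PHC-level ICC 0.1 for the sample-size calculation.

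**Assumptions.** The article gives no significance level for the preliminary tests, so I take a nominal two-sided 5%. It gives no ICC for baseline variables or for attrition, so I show a range.

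**Step 1: the plan's own design effect.** After 20% attrition there are 1250 × 0.8 = 1000 per arm, or 40 per PHC. The design effect is 1 + (40 − 1) × 0.1 = 4.9, and 1000/4.9 = 204, the stated effective size per group. Three measurements with a repeated-measures ICC of 0.5 give 204 × 3/[1 + (3 − 1) × 0.5] = 306, also as stated. The sample-size calculation therefore uses the very correction that the preliminary tests lack.

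**Step 2: between-arm baseline tests.** With m participants per PHC, DEFF = 1 + (m − 1) × ICC. The chance rejection rate of a test that ignores clustering is 2 × [1 − Φ(1.96/√DEFF)].

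| m | ICC | DEFF | Rejection rate at nominal 5% |
|---|---|---|---|
| 50 | 0.1 | 5.90 | 42.0% |
| 50 | 0.05 | 3.45 | 29.1% |
| 50 | 0.02 | 1.98 | 16.4% |
| 50 | 0.01 | 1.49 | 10.8% |
| 50 | 0 | 1.00 | 5.0% |
| 40 | 0.1 | 4.90 | 37.6% |

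For the first row, √5.9 = 2.429, 1.96/2.429 = 0.807, and the two-sided tail area is 0.420. At a nominal 2.5%, that row would give 35.6%.

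**Step 3: check by simulation.** I simulated 25 against 25 PHCs with 50 participants each, ICC 0.1 and no true difference. ANOVA rejected in 42.6% of runs, Kruskal-Wallis in 40.5% and chi-square in 42.1%. A t-test on PHC means rejected in 4.5% to 5.8% of runs over ICCs from 0 to 0.1.

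**Step 4: the two attrition comparisons.** These were simulated with 20% attrition that does not depend on arm. The demographic comparison uses a baseline variable with ICC 0.1.

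| Assumed attrition ICC | Attrition by arm (chi-square) | Completers v non-completers on the baseline variable (ANOVA) |
|---|---|---|
| 0 | 4.8% | 4.6% |
| 0.02 | 17.5% | 5.9% |
| 0.05 | 29.0% | 7.6% |
| 0.1 | 42.6% | 10.0% |

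The last column stays low because completers and non-completers are found in the same PHCs, so most of that contrast lies within clusters.

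**The case against.** Five points can be made on the other side.

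- **The ICC is borrowed.** The value 0.1 is a planning value for the outcome. Age, sex and other baseline variables may cluster less. This stands: 42% is what follows if a variable clusters that strongly, not an expected rate for every variable. Even at 0.01, though, the rate is about twice nominal.
- **Not every comparison is affected.** A reader might infer that about 40% of all balance and attrition comparisons will be falsely significant. The working does not support that. Completer against non-completer comparisons of demographics are nearly unaffected, and attrition by arm is inflated only if attrition clusters.
- **The primary result is protected.** The primary models include PHC, and no hypothesis or decision rule depends on these tests. This stands.
- **No link to covariates is stated.** A reader might infer that significant imbalance triggers adjustment, because the covariate rule is open. The article does not say so, and a covariate list is commonly left to the analysis plan, so its absence is not a finding.
- **An observed imbalance is a real difference in the sample, and looking for it is sensible.** This also stands. What is wrong is the p-value, which misstates how unusual the difference is when PHCs are randomised. A test with a false-positive rate this high is also a poor way to detect a genuine recruitment difference.

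**Conclusion.** The point holds for two comparisons: baseline variables between arms, and attrition by arm. For the first, the chance rejection rate at nominal 5% is about 42% at an ICC of 0.1, and 29%, 16% and 11% at 0.05, 0.02 and 0.01. For the second, it runs from about 5% with no clustering of attrition to about 43% at an attrition ICC of 0.1. These figures assume equal PHC sizes of 50 and a 5% level; apart from the outcome value of 0.1, the ICCs are assumptions.

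The documents do not support the stronger conclusion that the primary estimate or its Type I error is compromised. This is an error in supporting analyses. It is worth correcting because it could mislead readers about balance and differential loss, and because the article already uses the right approach elsewhere.

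**What to change.** In the opening paragraph of Statistical analyses:

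1. Describe arm balance with summaries by arm and standardised differences, without p-values. If tests are wanted, use PHC-level tests or mixed models with a PHC random intercept.
2. Test attrition by arm with a logistic model that has a PHC random intercept, as the Screening section already does for retention, or with a PHC-level test.
3. State that unadjusted balance p-values will not be used to choose covariates.

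The cost is a few sentences of wording. No data collection, sample size or primary model changes. The completer against non-completer comparisons of demographics could stay nearly as they are, though a PHC term would do no harm.

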#### Screening

To test the hypothesis that, compared to standard screening, enhanced screening will result, on an average, in more people being identified as co-morbid for CMD and CVD/DM during the confirmatory testing at the PHC, we will use a Poisson regression model - or in case of over dispersion, a negative binomial model - with PHC as the unit of analysis, and population size in the catchment area of the PHC included as an offset.

Secondary analysis will explore subsequent linkage and retention in care of enrolled participants first screened at the community health fairs compared to those first screened at PHC. These participants will be compared by examining the proportion of participants who started treatment both by the 6 week follow-up, as well as the proportion retained throughout the study. We will use a mixed-effects logistic regression model with a random intercept for PHC.

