### Setting and randomization

This study is conducted in collaboration with 50 PHCs in rural Ramanagara district of Karnataka state in southern India, each PHC serves a population of 30,000. A typical PHC has a medical officer, pharmacist, staff nurses, female multipurpose health workers (auxiliary nurse-midwives), male multipurpose health workers, ASHA workers, a laboratory technician/assistant, driver and helpers. It includes both outpatient and inpatient areas with four to six beds, as well as space for counseling, minor emergencies, a labor room, a pharmacy and a laboratory. The PHCs were assigned an identification number, and 25 PHCs were randomly assigned by the study statistician using a pseudo-random number generator to the enhanced screening arm linked to community health fairs and the remaining 25 were assigned to the standard screening arm. Subsequently, half of the enhanced screening and standard screening PHCs were randomly assigned to the collaborative care arm and the remaining half was assigned to the standard care treatment condition (Fig. 1). Participants randomized to the intervention group will be stratified by gender. While participants and intervention staff are not blinded, assessment staff are blinded to group assignment.

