### Enhanced screening vs standard screening conditions

The “enhanced” screening condition is implemented in 25 of our 50 PHC catchment areas, allowing us to examine whether the added community-based screening through community health fairs a) increases identification of patients with co-morbid diagnosis (Table 1); and b) improves linkage to and retention in care, compared to co-morbid patients identified via standard PHC-based screening. Specific recruitment procedures for each setting are described below, followed by common screening procedures and tests.

**Table 1 Tab1:** Initial and Confirmatory Screening Criteria

Screening stage	Inclusion criteria at each stage
Initial Screening Inclusion Criteria *Enhanced screening (health fair or PHC)* *Standard screening (PHC only)*	*Age:* 30 years or older *Mental competency:* Modified Short Blessed Cognitive Test [103] score ≤7 *General psychological distress*: The Kessler-10 [81] score ≥6 *One or more of the following cut-off measures for diabetes, hypertension, and/or CVD:* • Capillary Blood Sugar ≥160 mg/dL • Blood pressure ≥ 140/90 mmHg • Possible Angina: Rose angina questionnaire [104]^a^ • Self-reported physician-diagnosed history of DM, hypertension or ischemic heart disease
Confirmatory Screening Inclusion Criteria (PHC only)	*Depression/anxiety*: The Mini-International Neuropsychiatric Interview (MINI) [82] *One or more of the following clinical measures for diabetes, hypertension, and/or CVD:* • Blood pressure ≥ 140/90 mmHg • Capillary blood sugar ≥160 mg/dL • Physician-diagnosed history of DM, hypertension or ischemic heart disease (patient must show prescription or medication) • Possible rose angina^b^
Exclusion Criteria	• not mentally competent to provide consent per the standard screener [103], answer to study measures and/or participate in the intervention. • Participants who do not provide contact information

^a^ Patients who screen negative for hypertension and DM, but have possible angina on the rose angina questionnaire will be invited to the confirmatory screening

^b^ Patients who screen positive on the rose angina measure at initial screening and positive on the MINI during the confirmatory screening, but negative on hypertension and DM are marked as tentatively enrolled on the confirmatory screening form. At the baseline assessment electrocardiogram and cholesterol to check for CVD will confirm eligibility

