At the enhanced screening PHCs, nurses and ASHA run health fairs in villages that are a part of our collaborating PHC catchment areas. Prior to conducting the fairs, ASHAs raise awareness and provide outreach of the upcoming health fair through announcements at community events and meetings, poster, brochures, and door-to-door visits to community members. One health fair is held per week during the five-week recruitment period. The health fair provides an opportunity for people in the community to receive a free health check-up.

Screening occurs in two phases, during the initial screening and confirmatory screening (Table 1). The initial screening is held at the health fair or at the associated PHCs in the enhanced screening condition and at the PHC only for the standard screening condition. Interested patients give written informed consent to study staff for the screenings, and those meeting the eligibility criteria during the initial screening are invited to a confirmatory screening at the PHC. Patients who meet the eligibility criteria during the confirmatory screening are invited to participate in the study. Eligible participants receive information about the study verbally as well as in written form if literate, including details about the intervention, study protocol, randomization process, time commitment and potential risks and benefits. Participants are informed that participation is voluntary, there are no negative consequences for refusing to participate, and that consent can be withdrawn at any time during the study without any repercussions. Participants receive a copy of the study information sheet and informed consent. Illiterate participants have an option of providing verbal consent or a thumb print. In those cases, a witness, unaffiliated with the study, also signs the consent form.

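### Linkage and retention (Aim 1b) are compared by place of first screening, not by randomised screening arm, so the contrast is open to confounding by care-seeking

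*Protocol article*

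**What the plan says.** The article's section on setting and randomisation allocates PHCs at random, 25 "to the enhanced screening arm linked to community health fairs and the remaining 25 were assigned to the standard screening arm". Half of each group was then randomised to collaborative care.

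The section on the two screening conditions says that running the enhanced condition in 25 of the 50 catchment areas lets the trial examine whether added fair screening "improves linkage to and retention in care, compared to co-morbid patients identified via standard PHC-based screening". It also says where screening takes place, with the last clause referring to the standard arm: "The initial screening is held at the health fair or at the associated PHCs in the enhanced screening condition and at the PHC only".

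The screening part of the statistical analyses handles two questions differently. Case identification is analysed with the PHC as unit, enhanced against standard, with catchment population as offset. For the other question, "Secondary analysis will explore subsequent linkage and retention in care", and the groups are "enrolled participants first screened at the community health fairs compared to those first screened at PHC". The outcomes are starting treatment by the 6-week follow-up and being retained throughout the study. The model is stated as follows: "We will use a mixed-effects logistic regression model with a random intercept for PHC". No term for screening arm or care arm, and no measure of care-seeking, is named there.

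**The concern.** Place of first screening is not the allocation. Every standard-arm patient is screened at a PHC, but so are some enhanced-arm patients. Which enhanced-arm patients fall on which side depends on whether they came to a village fair or presented at the clinic. The abstract itself describes the comparator as people screened after presenting at a PHC, that is, people already in contact with care. Such contact plausibly predicts starting and staying in treatment, which are the outcomes.

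A random PHC intercept deals with clustering. It does not deal with this self-selection, and inside an enhanced PHC the comparison is wholly between patients who sorted themselves.

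At stake is the second half of Aim 1. A difference by place could be read as an effect of health fairs when it reflects who attends them, or selection could mask a real effect. The randomisation that could support a claim about adding fairs is not used for this question.

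**Working it through.** The article states no rate, power or sample size for linkage or retention, so there is no figure to reproduce. The check has two parts.

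**1. Is place the same as arm?** No, from the article's own description:

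| Randomised arm | First screened at fair | First screened at PHC |
|---|---|---|
| Enhanced (25 PHCs) | fair group | PHC group |
| Standard (25 PHCs) | none | PHC group |

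Take the planned 50 participants per PHC, so 25 × 50 = 1250 per screening arm. Let f be the share of enhanced-arm enrolees first screened at a fair (not given; range assumed). The fair group has 1250f patients and the PHC group 2500 − 1250f. The enhanced arm's share of the PHC group is (1 − f)/(2 − f):

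- f = 0.25: 937.5/2187.5 = 43%
- f = 0.50: 625/1875 = 33%
- f = 0.75: 312.5/1562.5 = 20%

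**2. What could selection alone produce?** Assume screening has no effect on any individual's chance of starting treatment, and that the chance is p_fair for fair-screened and p_PHC for PHC-screened patients. All rates are assumptions.

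- By place: difference = p_fair − p_PHC, whatever f is.
- By arm, among the enrolled: [f·p_fair + (1 − f)·p_PHC] − p_PHC = f·(p_fair − p_PHC).

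| p_PHC | p_fair | By place (points) | Odds ratio by place | By arm, f = 0.25 | f = 0.50 | f = 0.75 |
|---|---|---|---|---|---|---|
| 70% | 60% | −10 | (0.6/0.4)/(0.7/0.3) = 0.64 | −2.5 | −5 | −7.5 |
| 70% | 50% | −20 | (0.5/0.5)/(0.7/0.3) = 0.43 | −5 | −10 | −15 |
| 60% | 70% | +10 | (0.7/0.3)/(0.6/0.4) = 1.56 | +2.5 | +5 | +7.5 |

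The sign follows the assumed direction of selection, which the article does not settle. The by-arm figure is smaller but not zero: an enhanced arm that enrols a different mix of people shows a different linkage proportion even if fairs change nobody's behaviour. In this simple model a true effect confined to fair-screened patients would be diluted by the same factor f. The gain from the by-arm contrast is therefore not only its smaller absolute bias. It also compares randomised groups of PHCs, so a difference can be attributed to the screening policy, including its effect on who is enrolled.

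**The case against.** The strongest reply is that the by-place contrast is deliberate and modest. It is labelled secondary and exploratory. The abstract words Aim 1 by place, so the analysis matches one of the article's own statements of the aim. Every enrolee, however first screened, had to attend confirmatory screening at the PHC and consent, so fair attendees who never reached the clinic are already excluded, which plausibly narrows any gap in care-seeking. Covariate choice is ordinary content for an analysis plan that is not shown.

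Much of this stands and limits the point. It does not dispose of it: the article fixes the comparison groups explicitly, they differ from the randomised ones, and its section on the screening conditions ties linkage and retention to the randomised enhanced condition.

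A reader might infer more than the document supports:

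- **That the result will be biased by a known amount.** The rates above are assumed and the direction is unknown. Open to confounding is as far as the text goes.
- **That place of screening is unbalanced on care arm.** Care arm was randomised within each screening condition, and nothing suggests that it determines where a patient is first screened.
- **That the screening randomisation is discarded altogether.** Case identification, the only screening hypothesis with a power statement, is analysed by randomised PHC.
- **That per-PHC counts of linked patients with a catchment offset would avoid conditioning on enrolment.** Linkage and retention are defined for participants, and 50 are planned per PHC. If every PHC enrolled 50 and 70% linked, each would contribute 50 × 0.70 = 35, however many cases the fairs found.

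**Conclusion.** The point holds, at moderate severity. The only analysis stated for linkage and retention uses a patient-selected exposure and mixes part of the enhanced arm into its comparator, although a randomised contrast is available. The possible distortion cannot be sized from the article. Under the assumed rates it runs from −20 to +10 points by place, and from −15 to +7.5 points by arm among the enrolled for f between 0.25 and 0.75.

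The conclusion rests on two things: that place of first screening varies within the enhanced arm, which the article says, and that prior contact with care may predict treatment start and retention, which is plausible but not shown. The case-identification analysis and the primary treatment analyses are not affected.

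**What to change.** Keep the planned mixed-effects logistic model with a random PHC intercept, and make randomised screening arm (25 against 25 PHCs) the main exposure, with care arm as a covariate. Report fair against PHC as a descriptive contrast labelled non-randomised.

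State the limits alongside it. The by-arm comparison is still among enrolled participants, and screening arm affects who is enrolled, so selection is reduced but not removed. An effect confined to fair-screened patients will be diluted. The outcome section also defines retention among those who started treatment, which adds a further step of selection after randomisation.

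A per-PHC count of patients linked or retained, with catchment offset, could be supplementary only if enrolment is not capped at about 50 per PHC. Even then it would measure case-finding and linkage together and should be described that way.

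The main change costs analysis wording only; the allocation, outcomes and model are already in place.
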